### Sample size

The sample size for the efficacy question was calculated using the co-primary outcomes based on a minimum clinically important difference (MCID) at primary endpoint allowing for power at 0.80 and a two-sided alpha at 0.05 and using a Bonferroni correction for the two tests. The co-primary outcomes are symptoms of depression (PHQ-9) and anxiety (GAD-7) at 3 months follow-up. Based on previously established MCID for these measures (PHQ-9, MCID 2.59, SD = 5.4; GAD-7, MCID 4, SD = 5.07) [55, 56] and assuming 20% follow-up attrition, the calculated sample sizes are *n* = 129 per arm and *n* = 41 per arm respectively, with the larger of these (n = 129 per arm) the one required to satisfy the power requirements for both co-primary outcomes after the Bonferroni correction, i.e. a total sample of *n* = 258.

However, to power the study for the development of an ITR, we followed the recent recommendation arising from machine learning stimulations, which suggested that at a power of 0.80 based on a two-sided alpha of 0.05, a sample of at least 300 patients per arm is needed to develop an ITR that can detect a clinically meaningful difference in remission rates (between 5 and 10%) assuming a baseline remission rate from depression of 30% from both treatments aggregated [57]. As such, we increased the sample size to 300 participants per arm as the minimum to obtain stable estimates and generate a reliable ITR. This sample size gives a power of greater than 99% to compare the efficacy of guided versus unguided i-CBT.

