### Study settings

We seek to recruit 720 participants from within UK universities. Because all aspects of the trial are conducted remotely, there is a single active central study site delivering the study, namely the University of Exeter, which provides the coordinated central hub through which participants will be screened, randomized, data collected, treatment offered, and follow-up assessments delivered.

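### The efficacy sample size of 129 per arm does not follow from its stated inputs (about 105), and the step from 300 per arm to the target of 720 is not derived

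*Protocol article*

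**What the plan says.** All inputs for the efficacy calculation are in the protocol article under Sample size. The error rates are set by "allowing for power at 0.80 and a two-sided alpha at 0.05 and using a Bonferroni correction for the two tests". The target differences and standard deviations are "PHQ-9, MCID 2.59, SD = 5.4" and "GAD-7, MCID 4, SD = 5.07". Loss to follow-up enters with "assuming 20% follow-up attrition, the calculated sample sizes are" 129 per arm for PHQ-9 and 41 per arm for GAD-7, "with the larger of these (n = 129 per arm) the one required to satisfy the power requirements for both co-primary outcomes", giving 258 in total.

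The next paragraph turns to the individualized treatment rule (ITR). It takes a minimum of 300 per arm from cited simulation work, and concludes: "we increased the sample size to 300 participants per arm as the minimum to obtain stable estimates and generate a reliable ITR". It adds that efficacy power at this size exceeds 99%. Attrition is not mentioned in this paragraph, and the section ends without a total above 600.

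Under Study settings the target is different: "We seek to recruit 720 participants from within UK universities". The Abstract also gives 720. The Statistical analysis plan section bases the primary analyses on participants with complete 3-month outcomes.

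**The concern.** There are two separate problems in one chain of numbers.

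First, a reader who puts the stated PHQ-9 inputs into the usual two-sample formula does not get 129, while the same inputs come within one or two of the GAD-7 figure. The two figures therefore cannot share one set of assumptions, although the text presents them as if they do. The paragraph on mediation in the Statistical analysis plan section also refers back to these sample sizes for its own power statement.

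Second, the ITR requirement, not the efficacy comparison, determines the size of this trial. The link between 300 per arm and 720 recruited is thus the justification of the recruitment target, and the article does not give it. If the 300 has to be met by participants with outcomes, the target falls slightly below the plan's own minimum at the plan's own attrition rate.

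**Working it through.** **Inputs (Sample size section).** Difference 2.59 and SD 5.4 for PHQ-9, so d = 2.59/5.4 = 0.480. Difference 4 and SD 5.07 for GAD-7, so d = 4/5.07 = 0.789. Two-sided alpha 0.05 with Bonferroni for two tests, so 0.025 each. Power 0.80. Attrition 20%. Allocation 1:1.

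**Step 1: completers per arm.** n = 2(z₁₋α/₂ + z_power)² / d², with z = 2.2414 and 0.8416.
- PHQ-9: 2 × (3.0830)² / 0.2300 = 82.6; t-test version 83.9.
- GAD-7: 2 × (3.0830)² / 0.6224 = 30.5; t-test version 31.8.

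**Step 2: allow for 20% attrition**, rounding completers up and dividing by 0.8.

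| Outcome | Stated per arm | Normal approximation | t-test |
|---|---|---|---|
| PHQ-9 | 129 | 83/0.8 → 104 | 84/0.8 → 105 |
| GAD-7 | 41 | 31/0.8 → 39 | 32/0.8 → 40 |

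GAD-7 reproduces to within two participants. PHQ-9 does not: it is 24 to 25 per arm too high (258 in total against 208 to 210).

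**Step 3: can one rule give both figures?** With a common alpha, power and attrition rule, the two sample sizes must stand in the ratio (0.789/0.480)² = 2.71 (t-test version 83.9/31.8 = 2.64). The printed ratio is 129/41 = 3.15. Settings that reach about 129 for PHQ-9 give the following for GAD-7:

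| Setting | PHQ-9 | GAD-7 |
|---|---|---|
| alpha 0.01, power 0.80, ÷0.8 (t-test) | 103.2/0.8 = 129.0 | 39.2/0.8 = 49.0 |
| alpha 0.025, power 0.80, attrition applied twice (normal) | 82.6/0.64 = 129.1 | 30.5/0.64 = 47.7 |
| alpha 0.025, per-test power √0.80 = 0.894, ×1.2 (t-test) | 107.3 × 1.2 = 128.7 | 40.5 × 1.2 = 48.6 |
| alpha 0.025, power 0.90, ×1.2 (normal) | 107.9 × 1.2 = 129.5 | 39.9 × 1.2 = 47.9 |

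None gives 41. At the stated alpha, power and attrition, 129 would need a PHQ-9 difference of about 2.32 or an SD of about 6.0, and neither is stated. Adjusting for baseline would lower the number, not raise it.

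**Step 4: effect on power.** With 129 randomized per arm, 129 × 0.8 = 103 complete, and PHQ-9 power at alpha 0.025 is 0.88 rather than 0.80.

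**Step 5: from 300 per arm to 720.**
- 2 × 300 = 600, and 600 × 1.2 = 720 exactly.
- Inflation that preserves 600 after 20% loss: 600/0.8 = 750 (375 per arm).
- Expected completers at 720: 720 × 0.8 / 2 = 288 per arm, which is 12 fewer than 300 (12/300 = 4%).
- Attrition at which 720 still leaves 600: 1 − 600/720 = 16.7%.

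**Step 6: efficacy power.** For PHQ-9 at alpha 0.025 it is 0.9999 at 300 per arm and 0.9998 at 288. GAD-7 power is higher still. The claim of more than 99% reproduces.

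**The case against.** The best defence of 129 is that the section sizes the trial for both co-primary outcomes together. If 0.80 is joint power over two independent tests, each needs 0.894. PHQ-9 then needs 107.3 completers, and multiplying by 1.2 gives 128.7, rounded up to 129. The same setting gives 40.5 for GAD-7, rounded up to 41 before attrition. This could be what was done. It stands as a reason not to assert how 129 arose, and as a reason to let the authors state their rule instead of simply imposing 105. It does not rescue the text: joint power is not mentioned, and attrition would have been applied to one figure and not to the other.

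On the ITR number, the section speaks of patients and participants per arm and never says evaluable. The simulation study behind the 300 cannot be checked here. If 300 means randomized, 360 per arm exceeds it. The complete-outcome rule is stated for the primary analyses, and imputation is left open as a secondary analysis. A condensed article might also leave a one-line attrition step to the full protocol. All of this stands, so the shortfall is conditional. Three things favour the evaluable reading: the exact factor of 1.2 between 600 and 720, the attrition allowance already made in the same section, and the fact that a prediction model learns from observed outcomes.

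A reader might go further and infer that only 240 per arm will have outcomes (300 × 0.8). The documents do not support that, because the target is fixed at 720, not 600. A reader might also infer that the mediation power statement fails because it refers back to these sample sizes. That has not been shown, and the planned trial is nearly three times the 258.

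**Conclusion.** The 129 per arm (258) is wrong as written. The stated inputs give about 105 (210), and no single rule among those tried yields both 129 and 41. This rests only on the section's own figures and a standard two-sample comparison of means. The error is conservative and is overtaken by the ITR requirement.

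The 720 is not derived from the 300 per arm. If 300 means participants with outcome data, which is likelier but unstated, the target is expected to deliver 288 per arm at 20% attrition, 4% below the plan's minimum. If 300 means randomized, the only defect is the missing step.

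It would be tempting to read this as an underpowered trial. It is not: efficacy power for the stated differences remains above 99% at 288 per arm, and a 12-per-arm gap against a rounded threshold does not by itself make the ITR unreliable. The point is worth correcting because these figures are the published justification for the size of the trial.

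**What to change.** In the Sample size section:
1. Replace 129/258 by about 105/210, or state the alpha, the power (per test or joint) and the attrition rule actually used, and apply the same rule to both outcomes.
2. Say whether 300 per arm counts randomized participants or participants with outcome data.
3. Show the step to 720. If 300 is evaluable, state that 720 is expected to give 288 per arm at 20% attrition, and 300 per arm at up to 16.7%, and describe the ITR's precision at that number. If 300 is randomized, give the reason for the additional 120.

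The cost is wording only. No extra recruitment or change of analysis is needed. The stated ITR sample may look slightly less favourable, and the efficacy claim is unaffected.

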### Statistical analysis plan

The primary analyses will be intention-to-treat (ITT) analyses [58] (i.e. all participants will be included in the analyses according to their randomized allocation irrespective of intervention adherence) and based on participants with complete outcome data at 3-month follow-up. Where necessary, we will adjust for baseline outcome scores and stratification variable (site). The primary inferential analyses will compare across trial arms for the primary and continuous secondary outcomes at 3 months follow-up, adjusted for baseline scores, using multilevel mixed-effect models, which enable us to examine nested hierarchies in the data (individual, intervention, university), across time (examining pre-to-post change), to capture dependencies in the data, to investigate individual trajectories (random intercepts, random slopes), and which have less restrictive assumptions re missing data.

For the purposes of precision models, we will first explore which pre-treatment measures moderate the differential effects of treatment condition. Because individual predictors are usually weak and underpowered, our primary approach will be to use composite models that combine individual moderators to produce ITRs that can guide the selection of treatments most likely to be helpful for individual students. The approach will follow precedents established for developing precision treatment models via cross-validated machine learning methods as used in similar studies [30, 59–61]. Such machine learning methods for estimating heterogeneity of treatment effects include extensions of the generalized random forest algorithm [62–64] and of the Super Learner algorithm [65, 66], an ensemble machine learning approach. We will use the generalized random forest algorithm [62–64], with the option to add machine learning approaches (including ensemble approaches) as necessary, to develop a model that best predicts the relative effectiveness of alternative interventions. The machine learning approach has been validated for developing effective composite models, e.g. developing preliminary ITR with *n* = 150 [57, 61] and has the advantages of avoiding the need to specify main effects correctly and allowing the data‐driven estimation of nonlinear and higher‐order complex interactions across predictors. The value of guided and unguided iCBT at the individual level will be quantified using a counterfactual approach estimating the attained improvement of the mean outcome under a treatment selection scheme that always selects the treatment option with the best predicted outcome compared to the mean outcome under balanced randomization, generating a difference score or a personalized advantage index [67].

Secondary analysis will be undertaken including:Complier Average Causal Effect (CACE) analysis [68, 69] to provide an estimate of a treatment effect accounting for pre-specified per-protocol adherence and compliance with the treatment, whilst retaining the benefits of randomization.The extent of missing data will be considered, and where necessary, in agreement with the Trial Steering Committee (TSC), imputation (e.g. doubly robust estimation combining propensity score models with multiple imputation to reduce risk of bias) will be used to adjust for loss to follow-up.Exploratory mediation analyses will be undertaken to gain insight into mechanisms that could explain the potential effect of the interventions on primary outcomes. We will use modern causal inference methods using structural equation modelling or parametric regression models to assess mediation effects [70]. For mediation analyses of longitudinal data, assuming ICC = 0.5, the sample sizes to achieve MCID calculated above can detect small effect sizes for mediators (β = 0.14) in RCTs (with up to 8 micro-repeated assessments), at power = 0.80. A series of models will be performed for each outcome, investigating the mediation effect of each mediator variable individually and the mediation effect of each mediator variable in an overall model combining all mediators. The mediation effect will be reported as the indirect effect of treatment via the specified mediator, with a 95% confidence interval and the proportion of the total intervention effect mediated. Analyses will include the use of instrumental variables to account for effects of unobserved confounding on mediators [68].In addition, the ITR analysis will include composite baseline predictors estimated using nested cross-validation machine learning methods, to assign each participant a predicted probability of adherence to self-guided i-CBT and a separate predicted probability of adherence to guided i-CBT. The use of such composite measures as predictors in developing the ITR will make it possible to distinguish heterogeneity in treatment effects due to predicting differential adherence versus differential effectiveness of the two interventions given adherence.The results of all models will be compared to primary analysis complete case ITT results.

Analyses will be undertaken by a statistician blinded to group allocation and using Stata v.17 and R 4.5.0.

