### Randomization, intervention delivery, and masking

Participants will be randomized (in a 1:1 ratio) to the two intervention arms. Randomization will be conducted automatically by means of a custom-built secure web service created and managed by the Exeter Clinical Trials Unit (ExeCTU), which interfaces with the trial database and which will be independent of the trial researchers. To promote balance across key participant characteristics across intervention arms, randomization will be stratified according to recruitment site (each of the six funded partner universities plus “other” university category for students directly recruited via social media advertising). Blocking will be used with a minimum block size of 4 and a maximum block size of 6, occurring at random to maintain concealment.

All the online recruitment and randomization will be automated and independent of trial researchers. The Exeter CTU EDC system will contact an unblinded team member (administrator/therapist) indicating when an individual [by study ID] has been randomized to the active intervention. This team member will then access the relevant details in the ExeCTU database and manually set up the participant in the i-CBT platform using administrator rights via the treatment platform dashboard. An email will also go to the participant from the clinically trained members of the team providing support to the i-CBT, indicating the condition to which they are randomized and informing them what to expect. These team members will also monitor if the participant has accessed the i-CBT platform and check if any difficulties arise to encourage sign-up.

All assessments will be routinely collected online using the EDC following automated reminders, without the involvement of researchers. Site researchers will be blind to treatment allocation and analyses will be undertaken by a statistician blinded to group allocation. Site researchers will prompt all participants to complete follow-ups by email, text, WhatsApp and telephone call if they do not respond to the automated email reminders, including as a final step seeking to ask participants to complete the primary outcomes only over the telephone with the researcher. Any unblinding in contact with a site researcher would be logged as a protocol deviation and only a researcher that remained blind will be able to prompt future follow-up from that participant.

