#### Primary outcome

The primary outcome measures will be the mean symptoms of anxiety (GAD-7) and depression (PHQ-9) at 3 months (primary endpoint) adjusted for baseline scores.

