#### Secondary outcomes

Secondary outcomes include the mean scores at 3 months adjusted for baseline scores: the Warwick-Edinburgh Mental Wellbeing Scale (WEMWBS) [47], a widely used and well-validated measure of wellbeing; PSWQ-S [40] and RRS-B [41] to measure worry and rumination; and the Work and Social Adjustment Scale (WSAS) [48], a frequently used measure of functioning with respect to work/education, home management, social leisure, private leisure, and close relationships, each rated from 0 not at all impaired to 8 severely impaired. The Brief Resilience Scale [49] will assess students’ self-reported resilience. A bespoke questionnaire will assess the mean use of university-based and non-university-based healthcare (including National Health Service) services, resources, and support during the 3-month follow-up period. Another bespoke questionnaire will ask participants to report on the actual academic marks and their academic targets for the previous year and whether they were satisfied with their academic progress.

Participants will be asked to complete brief measures each week for 8 weeks after randomization to provide potential mediators of change: a two-item measure of depression (PHQ-2) [50]; a two-item measure of anxiety (GAD-2) [51]; a single-item measure of stress over the last week (scored 0 none to 4 very severe); six items from the Cognitive and Behavioural Response to Stress Scale [52] assessing the frequency and usefulness of use of cognitive reinterpretation, behavioural activation, and relaxation or meditation strategies; 3-item adaptations of the automaticity component of the Self-Report Habit Index [53] focused on assessing the extent to which worry and problem-solving respectively are each a habit (e.g. “something that I do automatically” “I do without thinking”) over the past 7 days; 2-items from the Self-Compassion Scale-short-form [54]; 2 items from the RRS-Brooding 5-item questionnaire [41]; a one-item measure assessing self-efficacy (“In the last seven days I feel better prepared to handle situations I could not handle before” rated using a seven-point Likert scale ranging from − 3 (“absolutely not true), 0 (“neither nor”) to + 3 (“absolutely true”) and a one-item measuring problem clarification (“In the last seven days, I understand myself and my problems better” rated using a seven-point Likert scale ranging from − 3 (“absolutely not true), 0 (“neither nor”) to + 3 (“absolutely true”).

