### Organization, quality assurance and data management

Research data will be automatically collected in a pseudonymized manner through an electronic data capture system licenced/programmed by Exeter Clinical Trials Unit (ExeCTU). In the first instance, all participants will be directed to the electronic data capture system to provide their data. Participants who respond to follow-ups by telephone will have their primary outcome data entered into the system by a site researcher, and this variation in data collection method will be recorded in the EDC. All data will be kept securely and confidentially and only accessed by specified researchers at the University of Exeter. The central data-management team will use de-identified backups for the monitoring of the overall progress and data quality, following a detailed study-specific Data Management Plan, which is available on request. Ultimately, a comprehensive de-identified dataset will be produced that includes all outcome data.

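### Students followed up by telephone give only PHQ-9 and GAD-7, so the complete-case rule leaves them out of the main comparison of each secondary questionnaire, and no stated analysis uses their known 3-month symptom scores to recover them

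*Protocol article*

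**What the plan says.** All places are in the protocol article.

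- **Follow-up by telephone.** Under Randomization, intervention delivery, and masking, site researchers prompt non-responders, "including as a final step seeking to ask participants to complete the primary outcomes only over the telephone with the researcher". Under Organization, quality assurance and data management: "Participants who respond to follow-ups by telephone will have their primary outcome data entered into the system by a site researcher". That section adds that the different mode of collection is recorded.
- **Outcomes.** Primary outcome: "The primary outcome measures will be the mean symptoms of anxiety (GAD-7) and depression (PHQ-9) at 3 months (primary endpoint"). Secondary outcomes: "Secondary outcomes include the mean scores at 3 months adjusted for baseline scores", followed by WEMWBS, PSWQ-S, RRS-B, WSAS and the Brief Resilience Scale, plus bespoke questionnaires on service use and academic results.
- **Analysis set.** Under Statistical analysis plan, the primary analyses are called intention-to-treat but are "based on participants with complete outcome data at 3-month follow-up". The same paragraph says that the primary inferential analyses "compare across trial arms for the primary and continuous secondary outcomes at 3 months follow-up", using mixed models, "which have less restrictive assumptions re missing data". The list of secondary analyses in that section refers back to the main analysis as complete-case ITT.
- **Imputation.** That list allows imputation where it is judged necessary and the Trial Steering Committee agrees. Its stated purpose is to adjust for loss to follow-up.

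**The concern.** For a student reached only by telephone, the secondary scales are missing by design: they are never asked. This student is not lost to follow-up, because two 3-month symptom scores are on file. A complete-case rule applied to a secondary scale discards the student and ignores those scores, although depression and anxiety at 3 months are likely to be among the best available predictors of wellbeing, worry, rumination and functioning at the same time.

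Three things are at stake. Precision of the secondary comparisons falls. Primary and secondary results rest on different samples. The secondary effects can also be biased if telephone response is related to symptoms and is more common in one arm. An arm difference is possible because only the guided arm has continuing practitioner support.

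**Working it through.** **1. Which data exist for a telephone-only responder**

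| Outcome at 3 months | Collected by telephone? | In the main complete-case comparison, judged per outcome? |
|---|---|---|
| PHQ-9, GAD-7 | yes | yes |
| WEMWBS, PSWQ-S, RRS-B, WSAS, Brief Resilience Scale | no | no |

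The mixed model does not change this. Restricting to complete cases gives up its advantage with missing data. A model of one secondary scale at baseline and 3 months also does not bring in the 3-month PHQ-9 or GAD-7.

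**2. Loss of precision**

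Inputs from the article: 720 participants (Study settings) and 20% attrition (Sample size). Taking attrition to mean no 3-month PHQ-9 or GAD-7, 720 × 0.80 = 576 students have these scores. The telephone-only share t among them is not given; 5% to 30% is assumed.

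- Number kept in a secondary comparison: N = 576 × (1 − t)
- Relative standard error: 1/√(1 − t)
- Standardised difference detectable with 80% power (two-sided 0.05, unadjusted, equal arms): 2.8016 × √(2/(N/2))

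| t | kept | left out | rise in SE | detectable difference (SD) |
|---|---|---|---|---|
| 0% | 576 | 0 | – | 0.233 |
| 5% | 547 | 29 | 2.6% | 0.240 |
| 10% | 518 | 58 | 5.4% | 0.246 |
| 20% | 461 | 115 | 11.8% | 0.261 |
| 30% | 403 | 173 | 19.5% | 0.279 |

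**3. Bias, simple form**

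Let telephone responders be k SD worse on symptoms than web responders, let the secondary score correlate ρ with symptoms, and let the telephone shares be tG (guided) and tU (unguided). The complete-case difference then departs from the all-responder difference by (tU − tG) × k × ρ, against guidance when tU > tG. All values are assumed.

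- Equal shares: 0.
- 10-point difference, k = 0.2, ρ = 0.5: 0.10 × 0.2 × 0.5 = 0.010 SD.
- 10-point difference, k = 0.5, ρ = 0.7: 0.10 × 0.5 × 0.7 = 0.035 SD.

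**4. Bias, by simulation**

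Assumptions: guided effect 0.20 SD on both PHQ-9 and the secondary score; within-scale correlation 0.5 between baseline and 3 months; correlation of the two scales 0.5 to 0.7; ANCOVA on both baselines; logistic probability of telephone-only response rising with 3-month PHQ-9 (slope 0.4 to 0.8 per SD).

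| Telephone share, guided v unguided | complete-case effect (SD) | shortfall from 0.20 |
|---|---|---|
| 15% v 15% | about 0.20 | about 0 |
| 5% v 10% | 0.179 to 0.194 | 0.006 to 0.021 |
| 10% v 20% | 0.163 to 0.186 | 0.014 to 0.037 |
| 15% v 25% | 0.161 to 0.186 | 0.014 to 0.039 |

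Imputing the missing secondary score from arm, baselines and 3-month PHQ-9 returned the full-data estimate in every setting. This is partly built in, because selection in the simulation depends on 3-month PHQ-9 and not on the unseen score. For scale, the standard error of such a comparison is about 0.075 to 0.081 SD, so these shortfalls are at most about half a standard error.

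**The case against.** **The imputation clause may already cover these students.** A student without a 3-month WEMWBS could be treated as lost for that outcome, so it would be too strong to infer that telephone responders are excluded from every secondary analysis. This stands. What remains is that the clause depends on a later judgement of need, is worded for loss to follow-up, and says nothing about using observed 3-month symptom scores.

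**The wording is only loose.** A reader might infer that telephone responders also leave the primary analysis, if complete means complete on every outcome. The documents do not support this. The call exists to obtain PHQ-9 and GAD-7 from these students, and the data are entered and flagged by mode. Outcome by outcome is the natural reading, and only a clarifying phrase is needed.

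**An arm difference in telephone response is conjecture.** The Background says that unguided self-help may have less engagement, which concerns the intervention and not the online assessments. Reminders, honorariums and prompting by blinded researchers are described without distinction of arm. This stands: the article does not show that the secondary effects will be understated. Even if they were, the error would run against the trial's own hypothesis.

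**The choice and ordering of analyses belong to the analysis plan.** This stands in part. Whether imputation should replace complete case as the main secondary analysis is a matter of preference, and it is not asked for here. The article does, however, state the complete-case rule and the telephone restriction, and their combined effect follows from its own text.

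**Conclusion.** The point holds in a limited form. As written, students who answer only by telephone are absent from the main comparison of each questionnaire-based secondary outcome, and no stated analysis is committed to using their 3-month PHQ-9 and GAD-7 to make good the gap. The co-primary comparisons are not affected under the per-outcome reading.

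The likely size is modest. Bias is near zero with equal telephone shares and about 0.01 to 0.04 SD on an assumed effect of 0.20 SD with a 5 to 10 point difference. The upper end needs a 10-point difference, the steepest selection and the highest correlation together. The loss of precision occurs whatever the balance between arms and grows with the telephone share. Every share, slope and correlation is an assumption; the article gives none. This is a worthwhile, inexpensive improvement to the secondary analyses and not a threat to the main conclusion.

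**What to change.** 1. In the opening paragraph of Statistical analysis plan, state that complete outcome data is defined outcome by outcome, so that PHQ-9 and GAD-7 obtained by telephone enter the primary analyses.
2. In the list of secondary analyses, commit unconditionally to a pre-specified multiple-imputation or joint-model analysis of each continuous secondary outcome in everyone with a 3-month PHQ-9 or GAD-7. Include arm, baseline scores and the observed 3-month PHQ-9 and GAD-7, and report it beside the complete-case result.
3. Settle this before telephone response by arm is known.

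The cost is a few sentences and modest programming, with no new data. The drawback is reliance on an imputation model: if telephone response also depends on the unseen secondary score, recovery will be incomplete. That is a reason to show both results side by side.
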